### Description of methods and data collection

a) Health facility assessments

Four HFAs [32] will be conducted over one month at four time periods between 2009 and 2012 to assess quality of care in study facilities. An initial pre-intervention assessment will be undertaken in both intervention and comparison health facilities to determine the comparability of the facilities. An immediate post-intervention assessment will be undertaken six months post-intervention to evaluate changes in quality of care. The third and fourth HFAs will be undertaken at 18 months and 30 months post-intervention, respectively. HFA components comprise a facility inventory, review of service statistics, interviews with health care providers, observations of client-provider interactions (CPIs), client exit interviews and client flow data. Data collection procedures for each component of these assessments are as follows:

i) Facility Inventory

An inventory will be taken of available resources required to deliver the intervention, including infrastructure, staffing numbers and skills mix, services provided, staff training undertaken, availability of equipment, commodities, forms and registers (client cards and notes), medications Researchers will request the head of the facility to guide them around to observe and record relevant information on a checklist.

ii) Interviews with healthcare providers

Structured interviews with health care providers will be conducted to determine their knowledge and skills for FP, PNC, HIV counseling and testing and other STI/HIV services; their understanding of organizational structure and related activities; their perceptions of barriers and operational challenges to FP/PNC clients’ acceptance of HIV counseling and testing; and their attitudes towards policy and procedural changes needed for provision of integrated care. All providers in the MCH-FP and ART units will be approached for interview in the 24 study facilities in Kenya, and 8 facilities in Swaziland. We anticipate between 3 and 6 providers from each facility will be interviewed.

iii) Observations of client-provider interactions

This component entails a structured non-participatory observation of health consultations, encompassing both the counseling process (how clients are treated and whether they actively participate) and the technical content of a consultation (provision of essential information and its technical accuracy). To reach a meaningful measure of quality of care with a relatively small sample size for the FP-HIV model, 18 consecutively sampled new FP clients and 18 revisit FP clients (assuming 6 clients for an average of three health providers in each facility) will be observed. For the PNC-HIV model in Kenya and Swaziland, 24 consecutively sampled postpartum women (between 6 to 8 postpartum women observed: within 48 hours of birth, between one to two weeks and around six weeks postpartum) per study facility. We acknowledge that observing client provider interaction may bias in a positive direction the results obtained on quality of care. We will spend more than one day at each site, so that the presence of the research team becomes more familiar and the behavior of the providers becomes more normative, furthermore over the three to four year data collection period the presence of researchers will become very familiar to the staff.

iv) Client exit interviews

Exit interviews will be held with each client who was observed to ascertain their perceptions of and satisfaction with the service received, as well as their SRH and HIV-related behaviors and fertility intentions.

v) Client flow assessment

A five-day assessment of service utilisation patterns will be conducted at each facility, biannually in Kenya, and annually in Swaziland, to measure: the total number of clients at each facility (per day); the service type being sought; the extent of service integration and referrals; and waiting times. Client data will also be captured including age, sex, and residence (proximity to the health facilities). All clients entering the facility for MCH services over the five-day period will be asked to participate, and given a client flow instrument by research assistants and/or service providers. Clients will carry the form throughout their consultations: every service provider seen will complete the form, indicating session start/end times, service(s) received and services referred for.

b) Prospective routine monitoring

This will involve collection of routine program monitoring data on utilization of family planning, postpartum/postnatal and HIV services. Forms will be used to extract client register data on a monthly basis for further analysis. Analysis of routine program data will contribute to answering the following questions: 1) what is the change in client profile pre- and post-integration (for instance, in terms of age, and sex)?, 2) does the rate of new clients accessing the services increase post-integration?, and 3) what are the changes in range of service uptake and client-profile pre- and post-integration across a range of SRH/HIV services.

c) Costing of service delivery across the different models

In each of the study facilities, the costs of delivering integrated SRH-HIV services will be measured both at baseline and endline, and the potential for efficiency gains will be assessed. Where feasible these cost data will be combined with an effectiveness analysis (with client and population level data) to estimate the cost-effectiveness of integrated services.

A periodic activity review (PAR) tool will be used to provide a mapping of how resources are combined to produce integrated HIV and SRH services in each study facility at baseline. The tool will include questions on facility characteristics, staffing types and levels, scope and number of services offered, clinical practice, descriptions of client flow, and overall description of how integration of services works from the provider’s perspective. Building on the PAR, the unit cost study will estimate the quantity and value of resources that are used to implement activities at facility level. Costing tools will be developed from the first round of data from the PAR, but will generally be based on UNAIDS costing guidelines: *The Costing Guidelines for HIV Prevention Strategies*[33].

A standard ingredients approach will be used. Bottom up methods will be used to estimate the direct costs of each service, and these will be combined with top-down method for the costs of overhead resources. In hospital settings, a step-down approach will be used for costs estimated through the top-down approach. The findings will be used to explore whether there are economies of scope and scale associated with the provision of an integrated package of SRH services, and to explore the relative efficiency of different models of provision. The cost data will be used to conduct an econometric analysis to estimate the impact of different cost drivers, including the extent of integration. This is the first time an economic study of this type will be used to evaluate integrated services [34].

d) Cohort study of clients

After the completion of the post-intervention HFA, two samples of clients accessing PNC and FP services (from intervention and comparison facilities) will be recruited and followed over a two-year period, interviewed up to 4 times. Various indicators will be monitored in these populations, including: condom and contraceptive use, fertility intentions, use of PNC and FP services, HIV status, unintended pregnancy, and SRH behaviors. To be eligible for inclusion in the FP-HIV study, the women will be aged 15 years and over, be revisit FP clients, be living in the catchment area of the health facility, and willing to give their informed consent to be interviewed. For the PNC-HIV model, the women will be aged 15 years and over, be clients attending a postnatal check for themselves and/or their infant (0–10 weeks), be living in the catchment area of the health facility, and willing to give their informed consent to be interviewed.

Cohort recruitment: Table 2 summarises the sample sizes that will be sought for the cohort studies. The minimum sample size will be based on 80% power to detect an increase in reported condom use (the key indicator/outcome that required the largest sample) from 5% to 10% in Kenya, with estimates of treatment effect derived from other studies in Kenya [18,20]; and from 13% to 20% in Swaziland, based on estimates from the 2006–2007 Swaziland Demographic and Health Survey (SDHS) [26]. The other outcome to be measured from these data is unintended pregnancies; since this required a smaller sample size it is covered within the condom use sample.

Cohort follow-up: Follow up interviews will be conducted at 6, 18 and 24 months after recruitment, either in the facility or at the woman’s home. If the woman is not located after three attempts, she will be considered lost to follow-up.

e) Household surveys

Community-based household surveys will be conducted with a randomly selected sample of men and women aged 15–49 years from the catchment communities surrounding the study facilities in Central Province (Kenya) and Manzini town in Swaziland. In Kenya, Thika district (intervention sites) and Nyahururu district (comparison sites) will be surveyed; in Swaziland, only Manzini (the largest urban settlement) will be surveyed where clinics included both intervention and comparison sites. The objective is to gain a representative view of service use around both intervention and comparison facilities and the population level need and demand for services. Use of PNC, FP or HIV/ STI-related services will be measured, as well as the use of informal or traditional health services. Community members will be asked standardized, and sex-specific, questions on access and use of services, attitudes to services, stigma, reasons for service use/non-use, as well as on unmet need for HIV testing, PNC and postpartum FP.

A three-stage cluster survey design will be employed. The primary sampling units (PSUs) will be census enumeration area (EAs), and the sampling frames will comprise the catchment areas of the relevant facilities (≤10km radius). Firstly, probability proportional to size (PPS) sampling will be used to randomly select EAs, with sampling frames derived from national censuses. It is estimated that between 25 and 40 EAs will be required to achieve the sample size in each survey district. Secondly, a random sample of households will be selected within each EA, using a systematic approach to achieve full geographic coverage of the EA based on estimated household numbers. Thirdly, one person will be randomly selected using a household roster to determine the sampling frame of eligible household members. The sample size calculations are displayed in Table 3, and were determined by measurement of the following key outcomes: (i) % respondents who have used a study facility (ii) % who can list the SRH/HIV services available at study facilities, (iii) % of female respondents using multiple services vs an integrated service, and (iv) % of female respondent’s not using modern contraception. The sample calculations were based on 80% power and a design effect (DEFF) of 2.0 to account for clustering, as well as accounting for non-response.

f) Qualitative study

In-depth interviews (IDIs) will be conducted to explore key study themes in greater depth. Respondents will be a sub-sample of cohort clients; health providers in study facilities; and a sub-sample of respondents from household surveys. The purpose of the in-depth interviews with the cohort clients is to explore experiences and motivations for use of services, facility switching, stigma and any other issues that arise after initial quantitative analysis. The purpose of the interviews with healthcare providers is to identify clinic- and provider-specific issues that may affect the delivery of integrated care. Interviews will aim to establish providers’ expectations regarding integration, to develop an in-depth understanding of their ongoing experience with providing integrated SRH-HIV services, attitudes towards PLWH, and to explore specific issues of workload, supervision and support, emotional strains, satisfaction and clinical records.

Interviews with community members are focused on men, since the facility-based client data are predominantly from women. Interviews aim to gain a deeper understanding of various issues, including reasons for service-use patterns, choice and perceptions of different facilities, reasons for non-use (including service-related stigma), and contraceptive and sexual health behaviours, including communication with partners and other community members about care-seeking decisions. The breakdown of the expected number of IDIs by different demographic groups is shown in Table 2.

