### Description of intervention

Table 1 provides a summary of the programmatic components and related activities that will strengthen and maintain the provision of integrated FP/PNC and HIV services; introduce new services and develop and strengthen the linkages between the services that were not integrated at intervention facilities. Existing standard services will be compared with the strengthened integrated FP and PNC service models shown in Table 1.

**Table 1 T1:** Summary of the interventions in FP and PNC sites

**Intervention component**	**Model 1: FP-HIV Kenya**		**Model 2: PNC-HIV**
Pre-existing standard services	·Counselling & provision of FP methods		·**Timing:** Usually delivered on discharge if hospital delivery, with 6 week check:
	·Dual protection counselling		·**Content:**
	·Screening of STIs		·Immunisation
	·HIV prevention counselling		·Growth monitoring/child welfare
	·Counselling on sex & sexuality, childbearing and PMTCT.		·FP at six weeks postpartum (on request from mother)
	·Refer FP clients for STI treatment/ syndromic management		(NB: this is what should happen according to the guidelines but rarely does at facility level)
	·Refer FP clients for HIV counseling and testing		
	(NB: this is what should happen according to the guidelines but rarely does at facility level)		
Strengthened or additional services introduced	·All clients receive strengthened Standard FP services using the Balanced Counseling Strategy Plus. This includes:		·**Timing:** within 48 hours of delivery, plus 7 day, and 6 week visit at facility
	·Discussion of fertility desires,		·**Content:**
	·Offering a range of FP methods		·Mother and baby physical examination to detect danger signs, complications, anomalies
	·Ensuring suitability of FP methods		·Infant feeding counseling
	·Condom promotion/provision		·Postpartum FP counseling and provision
	·STI and HIV risk assessment		·Screening for cervical cancer (at 6 weeks)
	·Check client HIV status		·HIV counselling & testing (mother and baby)
	·HIV counseling and testing		·HIV treatment prophylaxis for
	·Screening for cancer of cervix (via /vili)		·mother and baby
	STI screening and management Arrange follow up appointments		Neonatal male circumcision (Swaziland only)
	**HIV negative clients** Health promotion Risk factor exposure Risk assessment (routine) for STI/HIV		

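### PNC cohorts: entry at any postnatal check and follow-up timed from recruitment let the intervention's added and strengthened early visits shift postpartum age at entry, and to some degree who is enrolled

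*Protocol article*

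**What the plan says.** Table 1 of the protocol article (Description of intervention) gives the two PNC services different timings. The pre-existing service is "Usually delivered on discharge if hospital delivery, with 6 week check". The strengthened service is "within 48 hours of delivery, plus 7 day, and 6 week visit at facility". A note under the pre-existing service adds that "this is what should happen according to the guidelines but rarely does at facility level".

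The cohort section (Description of methods and data collection, part d) sets the start of recruitment: "After the completion of the post-intervention HFA, two samples of clients accessing PNC and FP services" are enrolled. Part a says of that facility assessment (HFA): "An immediate post-intervention assessment will be undertaken six months post-intervention".

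PNC cohort women must "be clients attending a postnatal check for themselves and/or their infant (0–10 weeks". Table 2 makes the sample consecutive but gives the window as within 12 weeks postpartum. On timing, "Follow up interviews will be conducted at 6, 18 and 24 months after recruitment".

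The section on data management and analysis compares cumulative probabilities of outcomes by the type of clinic that served the woman at recruitment. It mentions potentially confounding variables in general terms. No part of the article fixes a common entry visit, sets cohort quotas by visit, or uses delivery as time zero.

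For the HFA, PNC consultations are observed "within 48 hours of birth, between one to two weeks and around six weeks postpartum". Table 2 plans equal numbers at the three times in each PNC facility.

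**The concern.** The intervention changes which postnatal visits exist, any such visit is an entry point, recruitment starts after the change, and the clock starts at recruitment. Two consequences follow. First, a woman met at day 7 in an intervention clinic may have a comparison-clinic counterpart who is first met at 6 weeks, so the same interview falls at different times after birth. Second, a woman who attends at day 7 but would not return at 6 weeks can be enrolled where the 7-day visit exists and may not be enrolled elsewhere.

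The cohort outcomes include condom use (which set the sample size), contraceptive use and unintended pregnancy. All can be expected to depend on time since birth, most strongly in the early months. A between-arm difference at the early interviews could then partly reflect postpartum age or enrolment pattern. The design is non-randomised and rests its plausibility argument partly on this contrast, so an arm difference created by enrolment weakens it.

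**Working it through.** **Step 1. Side by side.**

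| Element | Comparison | Intervention |
|---|---|---|
| Early contact | Discharge check if hospital delivery | Visit within 48 hours |
| 7-day visit | Not listed | Listed |
| 6-week visit | Listed | Listed |
| Cohort entry | Any postnatal check, mother and/or infant | Same |
| Time zero for interviews | Recruitment | Recruitment |

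The 7-day visit is the only wholly new contact. The 6-week visit is common to both arms. The article gives no figures on the visit at which women will be recruited.

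**Step 2. Size of the time shift (shares assumed).** Take early entry as week 1 and late entry as week 6, 5 weeks apart. With early shares *a* (intervention) and *b* (comparison), the mean gap in postpartum age is 5 × (*a* − *b*) weeks, and it is the same at every interview.

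| *a* | *b* | Gap (weeks) | Share of 26 weeks | Share of 104 weeks |
|---|---|---|---|---|
| 25% | 0 | 1.25 | 4.8% | 1.2% |
| 50% | 0 | 2.5 | 9.6% | 2.4% |
| 75% | 0 | 3.75 | 14.4% | 3.6% |
| 100% | 0 | 5.0 | 19.2% | 4.8% |
| 50% | 25% | 1.25 | 4.8% | 1.2% |
| 50% | 50% | 0 | 0 | 0 |

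The last two rows allow for comparison women enrolled at the discharge check. For one pair of women, entry at day 7 puts the 6-month interview at about 6 + 0.2 = 6.2 months postpartum; entry at 6 weeks puts it at about 6 + 1.4 = 7.4 months. The entry window caps any gap at 10 weeks, or 12 under Table 2.

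**Step 3. What a shift could do to condom use (slope assumed).** Suppose use changes by *r* percentage points per postpartum month. The spurious difference is *r* × gap / 4.345, with 4.345 weeks to the month.

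- Gap 2.5 weeks: *r* = 1 gives 0.6 points; *r* = 4 gives 2.3 points.
- Gap 5 weeks: *r* = 1 gives 1.2 points; *r* = 4 gives 4.6 points.

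The planned effects are 10 − 5 = 5 points (Kenya) and 20 − 13 = 7 points (Swaziland). If use rises with time since birth, the earlier-entering intervention arm looks worse than it should; if use falls, it looks better. The article supports no value of *r*, and a constant slope is least credible late in follow-up.

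**Step 4. Selection.** This cannot be sized from the document. Unlike the time shift, it does not shrink as follow-up lengthens.

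**Step 5. HFA.** Equal quotas at the three times hold the visit mix constant in every facility if they are filled. A score pooled over visits is affected by visit mix only if a stratum falls short. The stratum most exposed is one to two weeks, which Table 1 does not list for the standard service and which no clinic had under that service before the intervention.

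**The case against.** **Early contact and a shared visit exist in both arms.** Standard care has a discharge check after hospital delivery. Entry is also open through the infant, and comparison PNC clinics were chosen on more than 50 infants a month at the 6-week immunisation. That visit may supply much of the recruitment in both arms. This stands: the contrast is one of degree, and the gap could be near zero. A reader might infer that comparison women are largely 6-week returners, or that the arms will certainly differ; the document does not show either.

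**The time scale and covariates belong in the analysis plan.** This stands in part. A condensed article need not name every covariate. But it does fix the entry rule and the timing of interviews, and those create the problem.

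**The size is assumed.** This stands. The shares and slopes above are illustrations, and by 24 months the time shift is small.

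**Enrolling or analysing only women seen at six weeks is no cure.** This stands. Six-week attendance is itself behaviour after the intervention began, and earlier contacts may change who returns. It would also cost numbers: Table 2 notes two facilities added in Swaziland because comparison client load was low, and it requires over-sampling of HIV-positive clients there. A six-week restriction is therefore suitable as a sensitivity analysis but not as the main contrast.

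**The HFA quotas already control visit mix.** This stands as long as they are filled. A reader might infer that the one-to-two-week stratum in comparison clinics will be empty or made up of unusual attenders. Nothing in the article says so, and its quotas assume that women will be found there.

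**Conclusion.** The point holds in a limited form, for the PNC cohorts only; the family planning cohort enrols revisit clients and is not affected. As written, the intervention can shift postpartum age at entry and, to some degree, the kind of woman enrolled, and nothing in the article neutralises this. The size is unknown. On assumed entry shares the mean gap runs from 0 to 5 weeks, which matters mainly at the first and 6-month interviews and amounts to at most about 5% of the 24-month follow-up. Whether it distorts condom use materially depends on a slope that the document does not give. The selection component may persist but cannot be quantified. Separately, the 0–10-week and 12-week entry windows contradict each other.

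For the HFA, the risk is conditional: pooled quality scores would be affected only if visit quotas are unevenly filled.

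**What to change.** 1. Record the entry visit and the infant's birth date for every PNC cohort woman, and report the entry-visit mix and postpartum age at recruitment by arm.
2. Analyse PNC cohort outcomes on time since delivery, with women entering the risk set at recruitment (delayed entry). Alternatively, adjust for or stratify by postpartum age at recruitment.
3. Add a sensitivity analysis limited to women enrolled around six weeks, the visit that both services list.
4. Reconcile the 10-week window in the cohort section with the 12-week window in Table 2.
5. For the HFA, compare quality scores within visit stratum, and do not pool over visits if the one-week quota is unfilled.
6. State as a limitation that selection by attendance remains: delivery-based time removes the clock difference but not differences in who was reached.

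The cost is small. Infant age is already needed to apply the entry criterion, so the extra work is mainly analysis. The six-week sensitivity analysis will be less precise and says nothing about women reached only at earlier visits.
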